# Assessing the efficacy, safety and utility of 6-month day-and-night automated closed-loop insulin delivery under free-living conditions compared with insulin pump therapy in children and adolescents with type 1 diabetes: an open-label, multicentre, multinational, single-period, randomised, parallel group study protocol

**DOI:** 10.1136/bmjopen-2018-027856

**Published:** 2019-06-03

**Keywords:** type 1 diabetes, closed-loop, artificial pancreas

## Abstract

**Introduction:**

Closed-loop systems titrate insulin based on sensor glucose levels, providing novel means to reduce the risk of hypoglycaemia while improving glycaemic control. We will assess effectiveness of 6-month day-and-night closed-loop insulin delivery compared with usual care (conventional or sensor-augmented pump therapy) in children and adolescents with type 1 diabetes.

**Methods and analysis:**

The trial adopts an open-label, multicentre, multinational (UK and USA), randomised, single-period, parallel design. Participants (n=130) are children and adolescents (aged ≥6 and <19 years) with type 1 diabetes for at least 1 year, and insulin pump use for at least 3 months with suboptimal glycaemic control (glycated haemoglobin ≥58 mmol/mol (7.5%) and ≤86 mmol/mol (10%)). After a 2–3 week run-in period, participants will be randomised to 6-month use of hybrid closed-loop insulin delivery, or to usual care. Analyses will be conducted on an intention-to-treat basis. The primary outcome is glycated haemoglobin at 6 months. Other key endpoints include time in the target glucose range (3.9–10 mmol/L, 70–180 mg/dL), mean sensor glucose and time spent above and below target. Secondary outcomes include SD and coefficient of variation of sensor glucose levels, time with sensor glucose levels <3.5 mmol/L (63 mg/dL) and <3.0 mmol/L (54 mg/dL), area under the curve of glucose <3.5 mmol/L (63 mg/dL), time with glucose levels >16.7 mmol/L (300 mg/dL), area under the curve of glucose >10.0 mmol/L (180 mg/dL), total, basal and bolus insulin dose, body mass index z-score and blood pressure. Cognitive, emotional and behavioural characteristics of participants and caregivers and their responses to the closed-loop and clinical trial will be assessed. An incremental cost-effectiveness ratio for closed-loop will be estimated.

**Ethics and dissemination:**

Cambridge South Research Ethics Committee and Jaeb Center for Health Research Institutional Review Office approved the study. The findings will be disseminated by peer-review publications and conference presentations.

**Trial registration number:**

NCT02925299; Pre-results.

Strengths and limitations of this studyThe study adopts an open-label, multicentre, multinational, randomised, parallel design: it includes a large group of children and adolescents across wide geographical locations.The trial adopts a 6-month follow-up period of hybrid closed-loop insulin delivery during unrestricted living.Participants in the two study groups will have an equal number of study visits.The study design excludes participants with recurrent incidents of severe hypoglycaemia or diabetic ketoacidosis during the previous 6 months, living alone and those with glycated haemoglobin <58 mmol/mol (7.5%) and >86 mmol/mol (10%) and with high or very low daily insulin requirements (total daily insulin dose ≥2 IU/kg/day or <15 IU/day).All participants are already pump users, somewhat limiting generalisability.

## Introduction

Type 1 diabetes is characterised by a deficiency of insulin caused by immunologically mediated damage to pancreatic beta cells, leading to raised blood glucose levels. Diabetes is one of the most common metabolic conditions. It is estimated that in 2017, 1 100 000 children and adolescents (0–19 years) worldwide had type 1 diabetes and that the number of newly diagnosed cases was over 130 000.^1^ The incidence rate in children is increasing by ~3%–4% per year with geographic differences.^1^ Earlier onset can result in diabetes complications appearing at a younger age, while dependence on lifelong insulin imposes a heavy burden on children, carers as well as healthcare systems.

Despite continuing progress, glycaemic control in children and adolescents with type 1 diabetes remains suboptimal.^2^ The achievement of recommended treatment goals is limited by the risk of hypoglycaemia. Even in those with the desired level of glycaemic control, non-physiological glucose excursions occur with periods of silent hyperglycaemia and hypoglycaemia.^3 4^ Individuals have blunted counter-regulatory responses to hypoglycaemia impairing recovery and increasing the threat of future episodes.^5^ Recurrent episodes may lead to hypoglycaemic unawareness, increasing the risk of severe hypoglycaemia.^6^ Hypoglycaemia has psychological consequences including the fear of hypoglycaemia with resulting maladaptive coping behaviours, such as excessive eating or under-insulinising, that may negatively impact glycaemic control.^7^

The development of continuous glucose monitoring has been a major advance.^8–11^ Sensor-augmented pumps combine real-time continuous glucose monitoring with insulin pump.^12^ Insulin pumps with low-glucose suspend feature have been shown to reduce hypoglycaemia.^13^ These systems, however, overall provide little or no automation to adjust insulin delivery to match glucose excursions.

An artificial pancreas (a closed-loop system) adjusts insulin automatically and represents a realistic treatment option for type 1 diabetes.^14^ The closed-loop control algorithm translates, in real-time, sensor glucose levels received from the glucose monitoring device and computes the amount of insulin to be delivered by the coupled insulin pump. Hybrid closed-loop systems automatically titrate insulin delivery, although the user manages insulin boosts at meal time.^15^ In 2017, the first closed-loop system entered clinical use in the USA.^16^

Closed-loop systems may improve glycaemic control while reducing the risk of hypoglycaemia.^17^ They have been evaluated in children and adolescents under controlled laboratory conditions^18–20^ and in home settings.^21–24^ Investigations in adults have also been conducted.^22 25 26^ Psychosocial assessments support acceptability and benefits of this therapeutic approach among children/adolescents and carers.^27^ Closed-loop systems are associated with increased time in near normoglycaemia and reduced time in hypoglycaemia and hyperglycaemia.^28^ So far, evaluations have been limited to 3 months.^22^

The present study will assess the efficacy, safety, utility and acceptability of 6-month day-and-night hybrid closed-loop insulin delivery during unrestricted living in comparison to usual care in children and adolescents with type 1 diabetes.

## Methods and analysis

### Overview

This trial adopts an open-label, multicentre, multinational, single-period, randomised, parallel group design, involving a 6-month home study period during which day-and-night glucose levels will be managed either by a closed-loop system (intervention group) or by insulin pump therapy (control group) (figure 1). We aim to recruit up to 150 children and adolescents aged ≥6 to <19 years with type 1 diabetes on insulin pump therapy (approximately equal proportion of those aged ≥6 to 12 years and 13 to <19 years, a minimum quota of 25% participants with baseline glycated haemoglobin >69 mmol/mol, >8.5%). Inclusion and exclusion criteria are summarised in box 1.

**Figure 1 F1:**
[figure not shown]
Study flowchart. HbA1c, glycated haemoglobin; CGM, continuous glucose monitoring.

Box 1Inclusion and exclusion criteriaSummary of inclusion criteriaAge ≥6 and <19 years.Type 1 diabetes as defined by WHO^34^ for at least 1 year.Use of an insulin pump for at least 3 months, with good knowledge of insulin self-adjustment by subject or caregiver as judged by the investigator.Using U-100 rapid acting insulin analogues Aspart or Lispro only.Willing to perform regular finger-prick blood glucose monitoring, with at least 4 blood glucose measurements per day.Screening glycated haemoglobin ≥58 mmol/mol (7.5%) and ≤86 mmol/mol (10%) based on analysis from local laboratory.Literate in English.Willing to wear continuous glucose sensor and closed-loop system at home.Willing to follow study-specific instructions.Willing to upload pump and glucose sensor data at regular intervals.Access to Wi-Fi.Living with someone who is trained to administer glucagon and is able to seek emergency assistance.Summary of exclusion criteriaLiving alone.Current use of any closed-loop system.Any other physical or psychological disease likely to interfere with the normal conduct of the study and interpretation of the study results, as judged by the investigator.Untreated coeliac disease, adrenal insufficiency or untreated thyroid disease.Current treatment with drugs known to interfere with glucose metabolism (eg, systemic corticosteroids, non-selective beta-blockers, monoamine oxidase inhibitors and so on).Known or suspected allergy to insulin.Clinically significant nephropathy (estimated glomerular filtration rate <45 mL/min) or on dialysis, neuropathy or active retinopathy (presence of maculopathy or proliferative changes), as judged by the investigator.Recurrent incidents of severe hypoglycaemia (>1 episode) during the previous 6 months (adolescents: severe hypoglycaemia is defined as an event requiring assistance of another person to actively administer carbohydrates, glucagon or take other corrective actions including episodes of hypoglycaemia severe enough to cause unconsciousness, seizures or attendance at hospital; children: severe hypoglycaemia is defined as an event associated with a seizure or loss of consciousness).Recurrent incidents of diabetic ketoacidosis (>1 episode) during the previous 6 months.Unwilling to avoid regular use of acetaminophen.Lack of reliable telephone facility for contact.Total daily insulin dose ≥2 IU/kg/day and <15 IU/day.Pregnancy, planned pregnancy or breast feeding.Severe visual or hearing impairment.Seizure disorder.Medically documented allergy towards the adhesive (glue) of plasters or unable to tolerate tape adhesive in the area of sensor placement.Serious skin diseases (eg, psoriasis vulgaris, bacterial skin diseases) located at places of the body likely to be used for localisation of the glucose sensor.Abusing illicit drugs, prescription drugs or alcohol.Use of pramlintide (Symlin), or other non-insulin glucose lowering agents including sulphonylureas, biguanides, dipeptidyl peptidase-4 (DPP4) inhibitors, glucagon-like peptide-1 (GLP-1) analogues, sodium-glucose cotransporter (SGLT)-1/2 inhibitors at time of screening.Shift work with working hours between 22:00 and 08:00.Sickle cell disease, haemoglobinopathy or has received red blood cell transfusion or erythropoietin within 3 months prior to time of screening.Eating disorder such as anorexia or bulimia.Employed by Medtronic Diabetes or with immediate family members employed by Medtronic Diabetes.

The University of Cambridge (UK) and Jaeb Center for Health Research (USA) are the coordinating centres. Clinical centres include:Addenbrooke’s Hospital, Cambridge, UK.Barbara Davis Center for Childhood Diabetes, Aurora, USA.Indiana University, Indianapolis, USA.Leeds Teaching Hospital, Leeds, UK.Nottingham Children’s Hospital, Nottingham, UK.Southampton Children’s Hospital, Southampton, UK.Stanford University, Stanford, California, USA.Yale University, New Haven, Connecticut, USA.

Cognitive, emotional and behavioural characteristics of participants and family members and their response to the closed-loop will be assessed gathering both quantitative (validated surveys) and qualitative data (focus groups). Written informed consent/assent will be obtained from all participants and guardians before any study-related activities.

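### Box 1 joins the two insulin-dose exclusion limits with *and*, which read literally excludes nobody, while the strengths and limitations list joins the same limits with *or*

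*Protocol article*

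**What the plan says.** The Overview of the methods section sends the reader to Box 1 for eligibility: "Inclusion and exclusion criteria are summarised in box 1". Under the exclusion criteria in that box, the line on insulin requirement reads "Total daily insulin dose ≥2 IU/kg/day and <15 IU/day".

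The list of strengths and limitations after the abstract describes the same restriction. There the design is said to exclude participants "with high or very low daily insulin requirements (total daily insulin dose ≥2 IU/kg/day or <15 IU/day". The two numerical limits match those in Box 1, and only the connective differs.

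Box 1 sets the age range at 6 to under 19 years and has no weight criterion. No other section repeats or clarifies the insulin rule.

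**The concern.** One limit is a floor per kilogram of body weight and the other is a ceiling on the absolute daily dose. With *or*, they cut off two opposite ends of the range of insulin requirement. With *and*, a participant must be at both ends at once, which is possible only at a very low body weight. An exclusion that no eligible person can meet has no effect.

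What is at stake is the definition of the study population. Box 1 is the article's statement of eligibility for eight centres in two countries, while the strengths and limitations list presents this exclusion as a restriction on the population studied. A reader judging to whom the result applies finds two rules that do not agree.

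**Working it through.** The documents state no figure for this point, so there is none to reproduce. The check is a direct inequality.

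**Inputs**
- Per-kilogram limit: 2 IU/kg/day or more (Box 1 and the strengths and limitations list).
- Absolute limit: below 15 IU/day (same two places).
- Age: 6 to under 19 years (Box 1).
- Body weight: not given. Assumption: every participant aged 6 or over weighs at least 7.5 kg. Weights from 7 to 70 kg were examined.

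**Step 1, joined by *and*.** Let *w* be weight in kg and *D* the total daily dose in IU. The criterion needs *D* ≥ 2*w* and *D* < 15 together. Some *D* satisfies both only if 2*w* < 15, that is, *w* < 15/2 = 7.5 kg.

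**Step 2, joined by *or*.** The excluded set is *D* < 15 together with *D* ≥ 2*w*, which contains possible doses at every weight.

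| Weight (kg) | 2 IU/kg/day in IU/day | Excluded under *and* | Excluded under *or* |
|---|---|---|---|
| 7 | 14 | 14 to <15 | every dose |
| 7.5 | 15 | none | every dose |
| 10 | 20 | none | <15 or ≥20 |
| 20 | 40 | none | <15 or ≥40 |
| 30 | 60 | none | <15 or ≥60 |
| 50 | 100 | none | <15 or ≥100 |

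At 7.5 kg the two limits meet and the joint set is already empty. It stays empty at every higher weight.

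**Step 3, use of the connectives elsewhere.** Where Box 1 joins two numerical limits with *and* in its inclusion criteria (age, and screening HbA1c from 58 to 86 mmol/mol), both must hold. Where it lists alternative grounds for exclusion, such as pregnancy and breast feeding, or visual and hearing impairment, it uses *or*. Usage within the box therefore favours the literal reading. The strengths and limitations list points the other way: it joins the HbA1c exclusions, below 58 and above 86 mmol/mol, with *and*, although no value can be both. There *and* must mean either limit.

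**Step 4, effect on the rest of the plan.** The stratification factors, the primary model, the per-protocol definition and the figures in the power calculation do not contain the insulin limits. The SD of 0.71% comes from 53 subjects of an earlier trial who were selected as meeting the eligibility criteria. The article does not say how the insulin limits were applied in that selection, and nothing suggests that the total of about 128 would change.

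**The case against.** The strongest reply is that no careful reader would be misled. The list speaks of "high or very low daily insulin requirements (total daily insulin dose ≥2 IU/kg/day or <15 IU/day", so the limits are plainly described as two extremes. The same sentence uses *and* loosely for two HbA1c exclusions that cannot both hold. On this view the Box 1 line simply names two excluded groups, and the impossibility of the literal reading is itself the clue. This makes a drafting slip the likely explanation. It does not remove the contradiction, because the usage within Box 1 favours the literal reading and no other section settles the matter.

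A second reply concerns consequences, and it stands in full. A reader might infer that centres have enrolled participants whom the study says it excludes, with a safety risk under automated insulin delivery. The documents do not support that. Box 1 is headed as a summary. The article appeared in June 2019, about two years after enrolment began in June 2017, so centres were screening from documents that are not shown here. Nothing shows that those documents carry the *and*.

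Nor can the number of people affected be estimated, since the article reports neither weights nor insulin doses.

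**Conclusion.** The Box 1 criterion is wrong as written, with minor severity. Taken literally it excludes 0% of participants weighing 7.5 kg or more, and it contradicts the strengths and limitations list, where either limit excludes. The only outside assumption is that nobody aged 6 or over weighs less than 7.5 kg.

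The finding is confined to an eligibility rule that the article states in two incompatible ways. Wrong enrolment and a safety effect are possible but not shown. The sample size and the planned analyses are not affected on anything the article states.

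**What to change.** Reconcile Box 1 with the strengths and limitations list so that the insulin-dose exclusion carries one operator in both places. Which rule the trial applies is for the sponsor to state from the full protocol. This review does not choose it, and notes only that the literal Box 1 wording cannot take effect in this age range.

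Then confirm that the full protocol and the eligibility documents used at the centres carry the reconciled wording. If they do, nothing further is needed. Only if they carry the Box 1 wording should participants already enrolled be checked against the reconciled criterion and any deviations listed.

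The cost is one word in the article and a short check of the eligibility documents. The check of participants arises only under that condition.

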### Study schedule

The study will comprise up to eight visits and six telephone/email contacts (see tables 1 and 2). The maximum study duration is 8 months.

**Table 1 T1:** Schedule of study visits/phone contacts when the participant is randomised to day-and-night closed-loop combined with low-glucose feature (intervention group)

	Visit/contact	Description	Start relative to previous/next visit/activity	Duration (hours)
Run-in	Visit 1	Recruitment visit: consent, HbA1c, screening bloods, urine pregnancy test, baseline surveys, blinded CGM training and insertion		1–4
	Visit 2	Review of baseline bloods, pump settings and CGM data; adjustment of treatment	2 weeks after visit 1 (+1 week); run-in could be repeated	1–2
Training period	Visit 3	Randomisation, repeat HbA1c if visit 3 and visit 1 are >28 days apart, urine pregnancy test, study pump training and initiation, competency assessment	May coincide with visit 2, within 8 weeks of visit 1	3–4
	Visit 3a	Real-time CGM training and initiation, competency assessment	Within 0–7 days of visit 3 (visit 3a may coincide with visit 3; training visits can be repeated)	2–4
CL + LGS intervention (6 months)	Visit 4*	CL initiation at clinic/home: data download, CL and low-glucose feature training, competency assessment, blinded CGM	4 weeks after randomisation (±1 week)	2–6
	Contact 1	Review use of study devices; study update	Within 24–48 hours after visit 4	<1
	Visit 5†	Review use of study devices; study update	1 week after visit 4 (±3 days)	<1
	Contact 2	Review use of study devices; study update	2 weeks after visit 4 (±3 days)	<1
	Contact 3	Review use of study devices; study update	1 month after visit 4 (±2 weeks)	<1
	Contact 4	Review use of study devices; study update	2 months after visit 4 (±2 weeks)	<1
	Visit 6	3 month visit: HbA1c, urine pregnancy test, data download, blinded CGM, surveys	4 months after randomisation (±2 weeks)	1–3
	Contact 5	Review use of study devices; study update	5 months after randomisation (±2 weeks)	<1
	Contact 6	Review use of study devices; study update	6 months after randomisation (±2 weeks)	<1
	Visit 7	Blinded CGM	2–4 weeks before planned visit 8	<0.5
	Visit 8	End of closed-loop treatment arm (6 months of CL): HbA1c, data download, surveys and focus groups; resume usual pump therapy	7 months after randomisation (±2 weeks)	1–3

*In-person clinic visit mandatory in USA only.

†Could be done via phone/email in UK. In-person visit mandatory in USA only.

CGM, continuous glucose monitoring; CL, closed-loop; HbA1c, glycated haemoglobin; LGS, low-glucose suspend.

**Table 2 T2:** Schedule of study visits/phone contacts when the participant is randomised to usual care (conventional or sensor-augmented insulin pump therapy) (control group)

	Visit/contact	Description	Start relative to previous/next visit/activity	Duration (hours)
Run-in	Visit 1	Recruitment visit: consent, HbA1c, screening bloods, urine pregnancy test, baseline surveys, blinded CGM training and insertion		1–4
	Visit 2	Review of baseline bloods, pump settings and CGM data; adjustment of treatment	2 weeks after visit 1 (+1 week); run-in could be repeated	1–2
Training period	Visit 3	Randomisation, repeat HbA1c if visit 3 and visit 1 are >28 days apart, urine pregnancy test, insulin pump refresher training, competency assessment	May coincide with visit 2, within 8 weeks of visit 1	3–4
Usual insulin pump therapy intervention (6 months)	Visit 4*	Initiation of standard therapy arm at clinic/home, glucometer download, recording of current insulin requirements, blinded CGM	4 weeks after randomisation (±1 week)	2–6
	Contact 1	Study update	Within 24–48 hours after visit 4	<1
	Visit 5†	Study update	1 week after visit 4 (±3 days)	<1
	Contact 2	Study update	2 weeks after visit 4 (±3 days)	<1
	Contact 3	Study update	1 month after visit 4 (±2 weeks)	<1
	Contact 4	Study update	2 months after visit 4 (±2 weeks)	<1
	Visit 6	3-month visit: HbA1c, urine pregnancy test, glucometer download, recording of current insulin requirements, surveys, blinded CGM	4 months after randomisation (±2 weeks)	1–3
	Contact 5	Study update	5 months after randomisation (±2 weeks)	<1
	Contact 6	Study update	6 months after randomisation (±2 weeks)	<1
	Visit 7	Blinded CGM	2–4 weeks before planned visit 8	<0.5
	Visit 8	End of standard pump therapy treatment arm (6 months): HbA1c, glucometer download, recording of current insulin requirements, surveys and focus groups, resume usual care	7 months after randomisation (±2 weeks)	1–3

*In-person clinic visit mandatory in USA only.

†Could be done via phone/email.

CGM, continuous glucose monitoring; HbA1c, glycated haemoglobin.

### Screening and baseline assessment

At screening, blood samples for full blood count, liver, thyroid function and anti-transglutaminase antibodies (with IgA levels if not done within previous 12 months) will be taken. Non-hypoglycaemia C-peptide, glucose and glycated haemoglobin will be measured and a urine pregnancy test in females of childbearing potential will be performed. Surveys investigating participants’ quality of life, psychosocial and cognitive functioning, and response to their current treatment will be distributed. Participants will be fitted with a blinded continuous glucose monitoring device (Libre Pro, Abbott Diabetes Care, Alameda, CA, USA) that will be worn during the run-in period at home for up to 14 days.

### Run-in period

During a 2–3 week run-in period, subjects will continue using their own insulin pump. Data obtained from blinded glucose sensors and pump downloads may be utilised for treatment adjustments. The run-in period may be extended/repeated if no or limited sensor data are available. At least 10 days of sensor data need to be collected. A longer run-in will not be used for additional fine-tuning of treatment adjustments.

